#### Randomisation

Schools are the unit of randomisation and will be randomly assigned to one of the three study conditions in a computer determined sequence using a clustered randomisation scheme.

#### Utilisation of the website

Use of the ‘Fun without Smokes’ website will be monitored by using web-logs of the intervention and the intervention + prompt condition. Every participant has a personal code (username). Based on this username web-logs can identify how often and when (date) a participant visits the website as well as which website components (e.g. reading tailored feedback letters, reading additional information, playing games, completing the questionnaire) he or she clicks.

#### Recruitment procedure

‘Fun without Smokes’ will be implemented in primary schools as a new programme offered via Regional Health Authorities (RHAs) in the Netherlands. A total of 31 RHAs in the Netherlands were invited through e-mail and telephone to participate in the recruitment of primary schools within their own region. Nine RHAs decided to participate in the active recruitment (information via telephone or school visits) and six were able to recruit primary schools in a passive manner (information via e-mail or newsletters). Maastricht University (UM) performed the same method in the regions of non-participating RHAs. Schools from all regions in the Netherlands will be included to reach a diverse sample of pupils. The intervention will be presented as an out-of-school programme, since the main part of the intervention takes place outside the school system. Over 3,500 Dutch primary schools were contacted for participation and 175 schools were willing to take part in the study (effectiveness rate = 5.0%). This procedure is illustrated in detail in Figure 3.

**Figure 3 F3:**
[figure not shown]
Recruitment of primary schools.

The criteria for inclusion are that primary schools want their final two grades (pupils aged 10-12 years) to participate in the study and the children have computers with Internet access at school and at home. Special education schools and schools using the prevention programme ‘I don’t smoke (either)’ [‘ik (r)ook niet’] were excluded. Schools that were interested in participation received an invitation letter and information brochure via the RHAs or UM. Furthermore, the programme was explained via telephone to the school principal. After two weeks, they were re-contacted by a member of the research team to discuss participation in the effectiveness study. When schools were interested in participation, agreement with inclusion criteria was checked.

Parents and children were informed about the procedure and goals of the study by means of a letter that children could take home for their parents. All students in grade seven of a participating school were included in the study unless they or their parents refused to be involved. By signing the informed consent letter and returning this to the research team, parents and children were able to deny participation before the start of the study. Additionally, they were able to withdraw participation at any moment by e-mail, telephone or in person during the entire study period.

#### Procedure

The baseline questionnaire (which is also the screening instrument for the tailored feedback messages) was completed during school hours under the supervision of a teacher, who also distributed to all participating children their personal log-in details in sealed envelopes. Non-participating children were instructed by the teacher to do something else. The same procedure will be employed for the one year follow-up assessment. The two year follow-up questionnaire will have to be completed at home, since by that time the children will have left primary school. For the two year follow-up the participants will be contacted via mail and e-mail inviting them to complete the web-based questionnaire.

After completion of the baseline and 12 months questionnaire, the children in the intervention groups will receive short summaries of the tailored feedback on their computer screen. Extended tailored advice will be sent one hour after completion of the web-based questionnaire as pdf attachment to the respondents e-mail address and will be posted on the website. In the next 12 months, children in the intervention groups can visit the website, to obtain new information or receive new advice as often as they want.

Six times a year participants in the intervention + prompt condition will be pro-actively prompted through e-mail and SMS to revisit the ‘Fun without Smokes’ website. The first three prompts will be sent 1, 2 and 3 months after the baseline measurement. The last three prompts will be sent 5, 7 and 9 months after baseline. In accordance with the prompts, some of the content of the website will be refreshed to address a new topic relevant for smoking prevention. This procedure will be repeated in the second year of the evaluation study. Participants in the intervention condition will not receive these messages, but will be able to revisit the website whenever they want during the 2-year follow-up period to view the same information as shown to participants in the intervention + prompt condition. The participants in the control condition will not have access to the ‘Fun without Smokes’ website.

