#### Questionnaire

The web-based questionnaire of the ‘Fun without Smokes’ program is an adapted version of the ‘Octopus’ questionnaire that assesses the predictors of smoking [9,22,23,38]. *Demographics* will be assessed in terms of: age, gender, name and location of the school, religion, ethnicity, family composition, pocket money, school performance, mobile phone number, e-mail address and socioeconomic status (SES). SES will be measured using the Family Affluence Scale (FAS), a scale to measure family wealth based on social and economic markers [39,40]. The FAS includes four questions concerning car ownership, number of holiday trips a year, number of computers at home and whether the respondent has his or her own bedroom. Answers will be combined in an index.

*Knowledge* of smoking will be assessed with six questions such as ‘When you smoke you have to cough more often’. The answer category includes ‘yes’, ‘no’ and ‘I don’t know’.

*Attitude* will be assessed using nine advantages (pros) and ten disadvantages (cons) of smoking. Participants have to complete the question ‘If I smoke…’ with answers such as ‘I will feel very mature - I will feel not mature’ (pro) or ‘I will become very ill - I will not become ill’ (con) on a four point scale. This procedure has also been supported in previous studies and indicated reliable scales [41].

*Social influence* will be measured using two different concepts: social norms and modelling. *Social norms* assess beliefs about smoking among parents, family and friends. Participants have to complete questions such as ‘My mother thinks that I…’ with a five point answering scale ranging from ‘definitely should not smoke’ to ‘definitely should smoke’. *Modelling* includes the smoking behaviour of parents, family and friends. In total, five questions will be included such as ‘Does your mother smoke?’ with a five point answer scale ranging from ‘often’ to ‘never’. The number of smokers in their environment will be assessed with three questions, for example, ‘How many of your friends smoke?’ a five point scale is used as answering option (almost all - almost none).

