### Strengths and limitations

Previous in-school smoking prevention programmes required much investment in time from the participating (primary) schools [45], leading to frustration and higher drop-out rates of participants or schools. The ‘Fun without Smokes’ programme is a web-based intervention, which requires only a very limited input and time from teachers, and thus meets the needs of schools to lower workloads involved in implementing smoking prevention programmes. A second strength is the design of the effectiveness study, since it assesses effects not only immediately, but also after 12 and 24 months. This allows testing both the short- and long-term effects of the ‘Fun without Smokes’ programme.

A possible limitation of the study is that smoking behaviour and other factors related to smoking are based on self-reports of youngsters, which might lead to measurement errors (i.e. social desirable answers). To avoid social desirable answers, we will guarantee full confidentiality to our participants. The validity of adolescent self-reported smoking has been shown to be high in accordance with biological indicators when measurement assures confidentiality [46]. Approximately 60% is expected to drop-out in the final measurement, since pupils are not connected to their primary school anymore. This drop-out percentage is taken into account in the sample size calculation. The large sample size will guarantee enough power for the evaluation study.

If the programme is proven to be effective, it will be a valuable tool for smoking prevention that can readily be implemented in primary schools in the Netherlands. This study will, furthermore, provide valuable information about the usability and additional effects of SMS and e-mail reminders in combination with a computer-tailored feedback programme.

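### The 24-month ever-smoking outcome expects about 60% loss, yet its stated invitation leaves out SMS, after programme contact that differs by arm

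*Protocol article*

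**What the plan says.** All references are to the protocol article.

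- **Setting at 24 months (Procedure).** Baseline and 12-month questionnaires are done in class under a teacher. For the last one: "The two year follow-up questionnaire will have to be completed at home, since by that time the children will have left primary school".
- **Invitation (Procedure).** "For the two year follow-up the participants will be contacted via mail and e-mail inviting them to complete the web-based questionnaire". The same route applies to every arm.
- **Expected loss (Strengths and limitations).** "Approximately 60% is expected to drop-out in the final measurement". One figure is given for all arms, and the article says the sample size allows for it.
- **Prompts (Procedure).** "Six times a year participants in the intervention + prompt condition will be pro-actively prompted through e-mail and SMS to revisit" the website, and "This procedure will be repeated in the second year of the evaluation study". For the intervention-only arm: "Participants in the intervention condition will not receive these messages". The control arm has no access to the website.
- **Letters (Content of the tailored feedback letters; Procedure).** These go to the two intervention arms, by e-mail and on the website.
- **Contact data (Questionnaire).** Mobile number and e-mail address are among the demographic items, with no restriction by arm.
- **Sizing (Sample size calculation).** Ever smoking 24 months after baseline is assumed to be 24% in control, 15% with the intervention and 8% with intervention plus prompts.

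**The concern.** The outcome on which the trial is sized is the one most exposed to non-response, and the randomised arms reach it with different histories of contact. A pupil prompted by e-mail and SMS for two years may be easier to reach than a control pupil, and may be more or less willing to answer. The Sample size calculation section counts the intervention arm's three expected website visits at the three measurement points. Answering the questionnaire is thus close to the behaviour that the prompts are meant to raise.

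If willingness to answer also depends on smoking, and does so differently by arm, the arms' responders are no longer comparable. Enlarging the sample restores precision but does not correct such a difference. Meanwhile a contact route that the trial already holds, the mobile number, is not named for the final measurement.

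**Working it through.** **Step 1. Contact before 24 months.** Prompts come at months 1, 2, 3, 5, 7 and 9, so 6 per year and 6 × 2 = 12 in total. If year 2 keeps the same spacing, the last falls at 12 + 9 = month 21.

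| Arm | Prompts | Letters by e-mail | Website access |
|---|---|---|---|
| Intervention + prompt | 12 | yes | yes |
| Intervention | 0 | yes | yes |
| Control | none stated | none stated | no |

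**Step 2. Expected responders.** With equal allocation, 3,240 / 3 = 1,080 pupils per arm. At 60% loss, 0.40 × 1,080 = 432 per arm answer. The 60% is the article's own expectation and has no derivation to reproduce.

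**Step 3. When does non-response bias the comparison?** Let p be true prevalence, and let rE and rN be the response of ever- and never-smokers. Prevalence among responders is

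p·rE / (p·rE + (1 − p)·rN).

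Dividing by rN shows that it depends only on p and k = rE/rN. In odds form, observed odds = k × true odds, so the crude odds ratio is multiplied by k(prompt)/k(control). Unequal response rates alone do no harm. With k = 0.7 in both arms, p = 0.24 gives 0.168 / (0.168 + 0.76) = 18.1% in each, whether overall response is 30% or 50%.

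**Step 4. Illustration with no true effect.** p = 24% in both arms (the article's control rate). Control response is 40% (from the 60% loss), assumed equal in ever- and never-smokers, so control shows 24.0%. Response in the prompt arm is assumed:

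| Never-smoker response | Ever-smoker response | Observed in prompt arm | Prompt − control |
|---|---|---|---|
| 50% | 50% | 0.120 / 0.500 = 24.0% | 0 |
| 50% | 45% | 0.108 / 0.488 = 22.1% | −1.9 points |
| 50% | 40% | 0.096 / 0.476 = 20.2% | −3.8 points |
| 45% | 50% | 0.120 / 0.462 = 26.0% | +2.0 points |
| 40% | 50% | 0.120 / 0.424 = 28.3% | +4.3 points |

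The planned differences are 24 − 15 = 9 points (control v intervention) and 15 − 8 = 7 points (intervention v prompt).

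**Step 5. Effect on the test.** Take k = 0.9 in control and 0.7 in the prompt arm, with 40% overall response in both. Observed prevalences are 22.1% and 18.1%, a false difference of 4.0 points. With 40 pupils enrolled per school (3,240 / 81), 16 remain after loss. The design effect at the stated ICC of 0.04 is 1 + 15 × 0.04 = 1.6, and the effective size is 432 / 1.6 = 270 per arm. The standard error is √[(0.221 × 0.779 + 0.181 × 0.819) / 270] ≈ 0.034, and a nominal 5% two-sided test rejects about 21% of the time. Reversing the two ratios gives the same figure in the other direction.

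**Step 6. What lower loss buys.** If 24% of responders have ever smoked and 60% are missing, the arm's true prevalence could lie anywhere from 0.24 × 0.40 = 9.6% to 9.6% + 60% = 69.6%. The width equals the missing share, so each point of loss avoided takes a point off it.

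**The case against.** The case on the other side is substantial.

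- **The follow-up procedure is identical in every arm.** A reader might infer that outcomes are collected differently by arm. They are not: all participants are invited, by the same route. What differs is the contact that came before.
- **Only e-mail is shared.** Prompts use e-mail and SMS; follow-up uses mail and e-mail. Post was not a prompt route in any arm.
- **The Background does not settle it.** It credits prompts with less programme drop-out and better adherence to interventions. A reader might take this as evidence that prompts raise response to a questionnaire at home, but the text does not say so.
- **The direction is open.** It is tempting to expect never-smokers to answer more readily after non-smoking prompts, which would flatter the prompt arm. Nothing in the article establishes this. The ever-smoker group also includes pupils who tried once and stopped.
- **Silence proves little.** The demographic list contains no postal address, but planned contact by mail implies that addresses are obtained somehow. Nor does the article say that control pupils hear nothing after month 12. Reminders and tracing may be in the full protocol, and missing-data methods belong in the analysis plan.
- **SMS adds a second route shared with the prompts**, and no reminder scheme can undo a contact history that is itself the tested contrast.
- **The 12-month assessment**, done in class, is much less exposed.

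All of this stands, and it limits the point to what the article actually fixes: a stated invitation route that omits an available means of contact at the measurement with the heaviest expected loss.

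**Conclusion.** The point holds as a weakness in a stated procedure, not as a demonstrated bias. Loss of about 60%, programme contact that differs across the three arms, and an invitation without SMS are all in the text. From these it follows that 24-month response could differ by arm. Bias requires in addition that the ever- to never-smoker response ratio differ between arms.

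Under the assumed response rates shown, with no true effect, the distortion runs from 3.8 points in favour of the prompt arm, through zero, to 4.3 points against it. These are illustrations and not bounds; the response rates by smoking status are assumptions. A claim that the plan will show a spurious benefit would go beyond the document. The point does not depend on whether the sample size is right. It is a cheap improvement.

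**What to change.** Amend the Procedure section so that the 24-month invitation and reminders go by mail, e-mail and SMS to all three arms, on one identical schedule, in identical wording kept separate from the website prompts. Have all pupils confirm or update their contact details during the 12-month classroom session, before they leave primary school.

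This should reduce overall loss, and with it both the room for differential non-response and the loss of precision. It does not remove the difference in contact history between arms.

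The cost is a small messaging charge, a contact-details page in the 12-month questionnaire, and a few study-reminder SMS to arms that otherwise receive none.

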#### Questionnaire

The web-based questionnaire of the ‘Fun without Smokes’ program is an adapted version of the ‘Octopus’ questionnaire that assesses the predictors of smoking [9,22,23,38]. *Demographics* will be assessed in terms of: age, gender, name and location of the school, religion, ethnicity, family composition, pocket money, school performance, mobile phone number, e-mail address and socioeconomic status (SES). SES will be measured using the Family Affluence Scale (FAS), a scale to measure family wealth based on social and economic markers [39,40]. The FAS includes four questions concerning car ownership, number of holiday trips a year, number of computers at home and whether the respondent has his or her own bedroom. Answers will be combined in an index.

*Knowledge* of smoking will be assessed with six questions such as ‘When you smoke you have to cough more often’. The answer category includes ‘yes’, ‘no’ and ‘I don’t know’.

*Attitude* will be assessed using nine advantages (pros) and ten disadvantages (cons) of smoking. Participants have to complete the question ‘If I smoke…’ with answers such as ‘I will feel very mature - I will feel not mature’ (pro) or ‘I will become very ill - I will not become ill’ (con) on a four point scale. This procedure has also been supported in previous studies and indicated reliable scales [41].

*Social influence* will be measured using two different concepts: social norms and modelling. *Social norms* assess beliefs about smoking among parents, family and friends. Participants have to complete questions such as ‘My mother thinks that I…’ with a five point answering scale ranging from ‘definitely should not smoke’ to ‘definitely should smoke’. *Modelling* includes the smoking behaviour of parents, family and friends. In total, five questions will be included such as ‘Does your mother smoke?’ with a five point answer scale ranging from ‘often’ to ‘never’. The number of smokers in their environment will be assessed with three questions, for example, ‘How many of your friends smoke?’ a five point scale is used as answering option (almost all - almost none).

*Self-efficacy* expectations will be assessed using ten items, in order to determine how easy or difficult it would be not to smoke in various situations. The questions are answered on a five point scale ranging from ‘very easy’ to ‘very difficult’ not to smoke [42]. ‘When others smoke it is…..for me not to smoke’ or ‘When my parents offer me a cigarette it is…for me not to smoke’ are examples of self-efficacy questions.

*Intention* will be measured differently for smokers and non-smokers. One question will assess smokers’ intention to stop smoking whereas non-smokers will be asked if they want to start (experimenting with) smoking (two questions). Intention will be measured on a five point scale with answering options ranging from ‘definitely yes’ to ‘definitely not’.

*Action planning* will also be differentiated for smokers and non-smokers. Smokers will be able to assess action plans on how to stop smoking, whereas non-smokers will be able to assess ways to refuse cigarettes. For both groups, action plans will be measured by five items, such as ‘I throw my cigarettes and lighter away’ for smokers or ‘I refuse that cigarette’ for non-smokers. These questions can be completed on a five point scale ranging from ‘totally agree’ to ‘totally disagree’.

*Smoking Behaviour* will be assessed by self-reports with the question: ‘Which statement describes your behaviour best?’ An internationally accepted algorithm [9,11,43,44] will be used as answering scale, ranking the following items: ‘I have never smoked, not even a puff’, ‘I have tried smoking once, but I do not smoke anymore’, ‘I have quit smoking, I have always smoked less than once a week’, ‘I have quit smoking after having smoked at least once a week’, ‘I try smoking once in a while’, ‘I smoke less than once a month’, ‘I do not smoke weekly, but at least once a month’, ‘I do not smoke daily, but at least once a week’ and ‘I smoke at least once a day’. Children will be categorised as non-smokers (never smoked a puff; have tried smoking, but not anymore; stopped smoking, after smoking less than once a week; stopped smoking, after smoking at least once a week) or as smokers (try smoking sometimes; smoke less than once a month; smoke at least once a month; smoke at least once a week; smoke every day). Smoking during the last 24 hours (‘Have you smoked during the last 24 hours?’), the past 7 days (‘Have you smoked during the past 7 days?’) and during the past month (‘Have you smoked during the past month?’) will be assessed as well. These questions will be assessed with a ‘yes/no’ answering scale. Additionally, a qualitative assessment will be made of the number of cigarettes smoked during the past week and weekend (‘How many cigarettes have you smoked during the last week/weekend?’).

#### Process evaluation

Pupils in both the intervention conditions will receive a process evaluation questionnaire to assess the tailored feedback letters. An invitation to fill out this (brief) web-based questionnaire will be sent via e-mail one day after they have received their third feedback letter. Children will be asked to indicate how many letters they have read and give an overall rating (1 = low to 10 = high) of the individual feedback letters. The process evaluation questionnaire will, furthermore, assess other aspects of appreciation, such as how attractive, pleasurable and comprehensible they thought the provided feedback was. These questions can be answered on four point scales. Examples of answering options are level of attractiveness (very nice - not nice), comprehensibility (very clear - not clear) and level of personalisation (very personal - not personal). After 12 and 24 months pupils in both the intervention conditions will be asked how many prompts they received (SMS and e-mail). Their opinions about these prompts will also be assessed. The amounts of visits will be qualitatively assessed by asking the pupils if they visited the ‘Fun without Smokes’ website and if they noticed the updates on the website. In addition, 12 and 24 months after baseline telephonic in-depth interviews will be held to assess qualitatively the evaluation of the programme among pupils.

